## 7.2 SCREENING

Screening period will start as soon as the written informed consent is signed, or the consent is obtained as per the local requirement for emergency inclusion procedure, the following examination will be performed before randomization:

- Informed consent form;
- Demographic data (age, gender...);
- Relevant Medical history;
- Eligibility criteria;
- Positive RT-PCR or antigenic test (test previously done accepted), or with a highly positive serology AND clear symptoms of COVID-19;
- Viral load test;
- Radiograph/ Chest CT scan (no more than 96hrs prior to randomization);
- Clinical evaluation / physical exam including height and weight (weight may be estimated by PI or delegate as patient's condition may prevent proper weighing at this time);
- Vital signs (BP, Pulse);
- Respiratory Distress Parameters
  - Respiratory Rate (RR),
  - Oxygen saturation (SpO2),
  - PaO2/FiO2
- 12-lead ECG;
- Local blood sample test;
- Urine or serum pregnancy test;
- Urinalysis;
- Concomitant medication;

## 7.3 BASELINE / RANDOMIZATION

Randomization will be performed automatically via the IxRS by the site. Detailed procedure will be described in the dedicated instruction manual. The following examination will be performed before randomization. General and specific examinations and tests that are part of the standard-of-care for Covid-19 management are not study specific and results can be used for the screening/eligibility assessment of the patients before the signature of the informed consent.

- Validation of eligibility criteria assessed during screening visit
- Vital signs (BP, Pulse); 1-time-point pharmacokinetics (baseline);
- Blood sample for Anti-glenzocimab antibodies (ADA) assessments will be collected and sent to the central laboratory;

- Soluble GPVI will be collected and sent to the central laboratory;
- Local blood sample test;
- Respiratory distress parameters:
  - Respiratory Rate (RR),
  - Oxygen saturation (SpO2),
  - PaO2/FiO2 (please refer to Appendix 3 for conversion);
- Chest CT-scan (to be repeated only if the previous one done more than 48 hrs prior to randomization);
- NEWS-2 and/or WHO scales;
- Concomitant medication;
- Recording of adverse events according to NCI-CTCAE;
- IxRS (Randomisation and Day 1 kit allocation).

The randomization visit should be performed within 24 hrs after the screening visit, once all eligibility criteria have been collected and checked.

#### **7.4 TREATMENT PERIOD: 1st INFUSION AND DAY-1 EVALUATION (3 hrs (+/-1 hr) after the end of the first infusion)**

Glenzocimab or the matching placebo is intended to be administered as a 6 hr IV infusion. The following examination will be performed:

- Clinical evaluation;
- Vital signs;
- 12-lead ECG;
- Pharmacokinetics: 3 sampling time-points:
  - Baseline, before the study drug administration,
  - 3 hrs after the beginning of the study drug administration,
  - 3 hrs after the end of the study drug administration,
- Local blood sample test;
- Respiratory distress parameters:
  - Respiratory Rate (RR),
  - Oxygen saturation (SpO2),
  - PaO2/FiO2;
- NEWS-2 and/or WHO scales;
- Optional Chest CT-scan;
- Urinalysis;
- Concomitant medication;
- Recording of adverse events according to NCI-CTCAE;
- IxRS for Day 2 kit allocation.

For the 1-day evaluation, a window of  $\pm 1$  hr is allowed.

### **7.5 TREATMENT PERIOD: 2nd INFUSION and DAY-2 EVALUATION (3 hrs (+/-1 hr) after the end of the second infusion)**

The following examinations will be performed:

- Clinical evaluation;
- Vital signs;
- 12-lead ECG;
- Pharmacokinetics: 3-sampling time-points:
  - Before treatment initiation (i.e. 24 hrs after first infusion initiation)
  - 3 hrs after the beginning of the study drug administration,
  - 3 hrs after the end of the study drug administration,
- Local blood sample test;
- Respiratory distress parameters:
  - Respiratory Rate (RR),
  - Oxygen saturation (SpO2),
  - PaO2/FiO2;
- NEWS-2 and/or WHO scales;
- Urinalysis;
- Concomitant medication;
- Recording of adverse events according to NCI-CTCAE;
- IxRS for Day 3 kit allocation.

For the 2-day evaluation, a window of  $\pm 1$  hr is allowed.

### **7.6 TREATMENT PERIOD: 3rd INFUSION and DAY-3 EVALUATION (3 hrs (+/-1 hr) after the end of the third infusion)**

The following examinations will be performed:

- Clinical evaluation;
- Vital signs;
- 12-lead ECG;
- Pharmacokinetics: 3 sampling time-points:
  - Before treatment initiation (i.e. 24 hrs after the second infusion initiation)
  - 3 hrs after the beginning of the study drug administration,
  - 3 hrs after the end of the study drug administration,

- Local blood sample test;
- Respiratory distress parameters:
  - Respiratory Rate (RR),
  - Oxygen saturation (SpO2),
  - PaO2/FiO2;
- NEWS-2 and/or WHO scales;
- Urinalysis;
- Concomitant medication;
- Recording of adverse events according to NCI-CTCAE.

For the 3-day evaluation, a window of  $\pm 1$  hr is allowed.

#### **7.7 DAY-4 EVALUATION (96 hrs)**

Day 4, is the Day where the Primary efficacy endpoint is recorded

The following examinations will be performed:

- Clinical evaluation;
- 12-lead ECG;
- Respiratory distress parameters:
  - Respiratory Rate (RR),
  - Oxygen saturation (SpO2),
  - PaO2/FiO2;
- NEWS-2 and/or WHO scales;
- Optional Chest CT-scan;
- Local blood sample test;
- Soluble GPVI;
- Concomitant medication;
- Recording of adverse events according to NCI-CTCAE.

For the 4-day evaluation, a window of  $\pm 1$  hr is allowed.

**7.8 DAY-5 EVALUATION (120 hrs)**

The following examinations will be performed:

- Clinical evaluation;
- 12-lead ECG;
- Local blood sample test;
- Concomitant medication;
- Recording of adverse events according to NCI-CTCAE.

For the 5-day evaluation, a window of  $\pm 1$  hr is allowed.

**7.9 DAY-7 EVALUATION**

The following examinations will be performed:

- Clinical evaluation;
- Vital signs (BP, Pulse);
- Viral load
- 12-lead ECG;
- Respiratory distress parameters:
  - Respiratory Rate (RR),
  - Oxygen saturation (SpO2),
  - PaO2/FiO2;
- NEWS-2 and/or WHO scales;
- Local blood sample test;
- Concomitant medication;
- Recording of adverse events according to NCI-CTCAE.

For the 7-day evaluation, these assessments can be performed at any daily visit at ICU.

**7.10 DAY-14 EVALUATION**

The following examinations will be performed:

- Clinical evaluation;
- Vital signs (BP, Pulse);
- Viral load
- 12-lead ECG;

- Respiratory distress parameters:
  - Respiratory Rate (RR),
  - Oxygen saturation (SpO2),
  - PaO2/FiO2;
- NEWS-2 and/or WHO scales;
- Local blood sample test;
- Urinalysis;
- Concomitant medication;
- Recording of adverse events according to NCI-CTCAE.

For the 14-day evaluation, a window of  $\pm 2$  days is allowed.

#### **7.11 DAY-20 EVALUATION**

The following examinations will be performed:

- Clinical evaluation;
- Vital signs (BP, Pulse);
- 12-lead ECG;
- Respiratory distress parameters:
  - Respiratory Rate (RR),
  - Oxygen saturation (SpO2),
  - PaO2/FiO2;
- NEWS-2 and/or WHO scales;
- Local blood sample test;
- Concomitant medication;
- Recording of adverse events according to NCI-CTCAE (version 5.0) and SAEs.

For the 20-day evaluation, a window of  $\pm 2$  days is allowed.

#### **7.12 DAY-40: END OF STUDY VISIT**

The following examinations will be performed:

- Clinical evaluation;
- Vital signs (BP, Pulse);
- RT-PCR test;
- Viral load test;
- 12-lead ECG;

- Respiratory distress parameters:
  - Respiratory Rate (RR),
  - Oxygen saturation (SpO2),
  - PaO2/FiO2;
- NEWS-2 and/or WHO scales;
- Urine or serum (β-hCG) pregnancy test;
- Local blood sample test;
- Blood sample for Anti-glenzocimab antibodies (ADA) assessments will be collected and sent to the central laboratory;
- Concomitant medication;
- Recording of adverse events according to NCI-CTCAE (version 5.0) and SAEs.

For the 40-day evaluation, a window of  $\pm 3$  days is allowed.

## 7.13 ASSESSMENTS AND PROCEDURES

### 7.13.1 Efficacy Assessment

Efficacy assessments will consist of evaluating respiratory distress parameters, two specific scales and chest CT-scans.

#### NEWS-2

NEWS2 is the latest version of the National Early Warning Score (NEWS), first produced in 2012 and updated in December 2017, which advocates a system to standardize the assessment of and response to acute illness (*see Appendix I*).

NEWS is based on a simple aggregate scoring system in which a score is allocated to physiological measurements, already recorded in routine practice, when patients present to, or are being monitored in, hospital. Six simple physiological parameters form the basis of the scoring system:

1. Respiration rate
2. Oxygen saturation
3. Systolic blood pressure
4. Pulse rate
5. Level of consciousness or new confusion\*
6. Temperature.

*\*The patient has new-onset confusion, disorientation and/or agitation, where previously their mental state was normal – this may be subtle. The patient may respond to questions coherently, but there is some confusion, disorientation and/or agitation. This would score 3 or 4 on the GCS (rather than the normal 5 for verbal response), and scores 3 on the NEWS system.*

A score is allocated to each parameter as they are measured, with the magnitude of the score reflecting how extremely the parameter varies from the norm. The score is then aggregated and uplifted by 2 points for people requiring supplemental oxygen to maintain their recommended oxygen saturation.

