**NEWS-2 scale**

NEWS2 is the latest version of the National Early Warning Score (NEWS) updated in December 2017. As the news-2 scale is not an interval scale, a categorical ordinal analysis will be performed. Thresholds on the aggregated score suggested by the Royal College of Physicians will be used to transform the NEWS-2 scale into a categorized scale (called hereafter the “categorized news-2 scale”). Further details on the thresholds will be provided in the SAP.

Missing values of the NEWS-2 scale not due to death will be replaced by the last available news-2 scale value before deriving the category of the categorized NEWS-2 scale. Missing values of the NEWS-2 scale due to death occurring prior to or on day D4 will be imputed in the highest category.

A descriptive analysis of each category (count and percentage) will be performed by treatment group at day D4.

The distribution of the categorized news-2 scale at Day D4 will be compared between groups with a Cochran-Mantel Haenszel test using modified ridit scores (i.e. categorical counterpart of the Wilcoxon test) and stratified by baseline categorized news-2 scale values.

The same analysis will be proposed at other time points (Days 1, 2, 3, 14, 20 and 40).

The distribution of outcomes on the categorized news-2 scale will also be described via plots (e.g., stacked bar plots representing the proportion of subjects in each category, by treatment arm, over time).

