## 18. APPENDICES

### Appendix 1: NEWS-2 Scale

| National Early Warning Score (NEWS)* |       |          |             |             |             |           |            |
|--------------------------------------|-------|----------|-------------|-------------|-------------|-----------|------------|
| PHYSIOLOGICAL PARAMETERS             | 3     | 2        | 1           | 0           | 1           | 2         | 3          |
| Respiration Rate                     | ≤8    |          | 9 - 11      | 12 - 20     |             | 21 - 24   | ≥25        |
| Oxygen Saturations                   | ≤91   | 92 - 93  | 94 - 95     | ≥96         |             |           |            |
| Any Supplemental Oxygen              |       | Yes      |             | No          |             |           |            |
| Temperature                          | ≤35.0 |          | 35.1 - 36.0 | 36.1 - 38.0 | 38.1 - 39.0 | ≥39.1     |            |
| Systolic BP                          | ≤90   | 91 - 100 | 101 - 110   | 111 - 219   |             |           | ≥220       |
| Heart Rate                           | ≤40   |          | 41 - 50     | 51 - 90     | 91 - 110    | 111 - 130 | ≥131       |
| Level of Consciousness               |       |          |             | A           |             |           | V, P, or U |

*Appendix 2: WHO COVID-19 Ordinal Scoring Scale*

| Patient State                          | Descriptor                                            | Score |
|-----------------------------------------------|--------------------------------------------------------------|--------------|
| Uninfected                      | No clinical or virological evidence of infection             | 0            |
| Ambulatory                      | No limitation of activities                                  | 1            |
|                                               | Limitation of activities                                     | 2            |
| Hospitalized
Mild disease   | Hospitalized, no oxygen therapy                              | 3            |
|                                               | Oxygen by mask or nasal prongs                               | 4            |
| Hospitalized
Severe Disease | Non-invasive ventilation or high-flow oxygen                 | 5            |

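### Section 7.13.1 scores new confusion 3 on NEWS-2, but the Appendix 1 chart has no entry for it, so an alert, newly confused patient totals 3 points less by the chart

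*Protocol*

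**What the plan says.** Protocol Section 7.13.1, under NEWS-2, lists six parameters. The fifth is "Level of consciousness or new confusion", and a note to it describes the newly confused patient: "The patient may respond to questions coherently, but there is some confusion, disorientation and/or agitation". The note then gives the score: "This would score 3 or 4 on the GCS (rather than the normal 5 for verbal response), and scores 3 on the NEWS system". For the scale itself the section refers the reader onward ("see Appendix I").

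The appendix is headed "Appendix 1: NEWS-2 Scale", but the title on the chart is "National Early Warning Score (NEWS" followed by a closing bracket and an asterisk. The row "Level of Consciousness" has two filled cells: A in the 0 column, and V, P or U in the right-hand 3 column. No cell mentions confusion.

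Section 9.1 lists NEWS-2 among the secondary efficacy endpoints. Section 11.5.1 cuts the aggregate score into categories and leaves the thresholds to the SAP. The Day 4 analysis is then: "The distribution of the categorized news-2 scale at Day D4 will be compared between groups", with a Cochran-Mantel-Haenszel test stratified by the baseline category. The same analysis is planned at Days 1, 2, 3, 14, 20 and 40. Values missing for reasons other than death take the last available score.

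**The concern.** The protocol gives two scoring instructions for one item of a listed endpoint, and they disagree for a recognisable kind of patient: alert, able to answer, but newly confused. By the section's own description this change can be subtle. The text gives it the maximum for the item; the chart, which is what a ward would have in hand, offers only the normal entry.

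Up to 11 sites in two countries (7 in France, 4 in Brazil) will score from this protocol. If some work from the text and others from the chart, the same patient can receive two different totals. The total feeds both the outcome category and, through the baseline value, the stratum in which the patient is compared. Because the last available score replaces a missing one, a wrong score can also carry forward to later days.

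**Working it through.** No power or sample-size formula is involved. The check is to score the same patient by each instruction.

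**Inputs.** All item points come from the Appendix 1 chart: respiration rate 12–20 = 0, 21–24 = 2, ≥25 = 3; oxygen saturation 92–93 = 2, 94–95 = 1, ≥96 = 0; supplemental oxygen = 2; temperature 36.1–38.0 = 0; systolic pressure 111–219 = 0; heart rate 51–90 = 0, 91–110 = 1. For consciousness, the chart gives A = 0 and V, P or U = 3, and Section 7.13.1 gives new confusion = 3. The chart does not spell out its letters; I read A as alert and the other three as reduced responsiveness.

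**Step 1: can the text's 3 points be obtained from the chart?** No. A patient who answers coherently fits none of V, P or U. The only cell left is A, worth 0.

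**Step 2: aggregate score.** Let S be the sum of all other items. The chart gives S + 0 and the text gives S + 3. The difference is 3 for every value of S. Three assumed patients, all alert and newly confused:

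| Assumed patient | S | Chart | Text |
|---|---|---|---|
| A: RR 26, SpO2 93, on oxygen, 37.5 °C, SBP 120, HR 100 | 3+2+2+0+0+1 = 8 | 8 | 11 |
| B: RR 22, SpO2 94, on oxygen, 37.5 °C, SBP 120, HR 80 | 2+1+2+0+0+0 = 5 | 5 | 8 |
| C: RR 18, SpO2 96, no oxygen, 37.0 °C, SBP 120, HR 80 | 0+0+0+0+0+0 = 0 | 0 | 3 |

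**Step 3: does the analysed category change?** If a higher category starts at score c, the category differs only when S < c ≤ S + 3. Patient A changes category only if a cut lies at 9, 10 or 11; patient B only if one lies at 6, 7 or 8; patient C only if one lies at 1, 2 or 3. The protocol does not state the cuts, so the step ends there.

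**Step 4: is the confusion entry the only mismatch?** It is not. Inclusion criterion 5 in Section 5.1.1, the primary endpoint in Section 8.1.1 and its restatement in Section 11.5.1 all refer sites to scale 2 of the NEWS-2 SpO2 item for conversion. The chart has a single oxygen-saturation row and no scale 2. The chart therefore lacks two features that the protocol itself attributes to NEWS-2. Together with the chart's title, this suggests that the wrong chart was inserted rather than that one cell was dropped.

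**The case against.** The best defence is that the chart is silent rather than contradictory. Nowhere does it say that a confused patient scores 0, and Section 7.13.1 supplies a specific written rule that fills the gap. A site that reads both has its answer, and nothing shows that sites will divide into users of the text and users of the chart. This stands as far as it goes: how sites will behave is not known. But the section itself points to the chart for the scale, and anyone scoring from the chart alone reaches 0 for this patient.

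The asterisk in the chart title may point to a note that did not survive in the text available to me. That remains possible, but the scoring row would still have no entry for confusion.

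A reader might also infer more than the protocol supports:

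- **That the analysed endpoint is off by 3 points.** It is not analysed in points. The 3 points apply to the aggregate, and the category may or may not move. Patients enter with respiratory distress, so some will already score high on the other items, and the extra points may leave them in the same category.
- **That a known share of patients is affected.** No frequency is given. An assumed 5 to 15% would mean 3 to 9 of 60 patients at a visit, but nothing in the protocol supports that range and the true number could be close to zero.
- **That the treatment comparison is biased.** Section 6.3.2 keeps investigators and site staff blinded, so inconsistent scoring has no reason to favour an arm.
- **That the eCRF takes a site-entered total and needs redesign.** The protocol does not describe how NEWS-2 is captured; components may already be recorded.

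NEWS-2 is also one of many secondary endpoints in an exploratory estimation study, and the primary endpoint does not use consciousness.

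**Conclusion.** The concern holds in limited form: the protocol is wrong as written, and the point is minor. For an alert patient with new confusion, the Appendix 1 chart gives an aggregate NEWS-2 score exactly 3 points below the score required by Section 7.13.1. This follows from the two current texts and rests only on reading A as alert.

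The effect on the results cannot be sized from the protocol, because it depends on the category thresholds, on how many patients are alert and newly confused at a visit, and on which instruction each site follows. What can be said is its kind: non-directional misclassification of a secondary endpoint and, where it occurs at baseline, of the stratum used in the test.

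**What to change.** Replace the Appendix 1 chart with one that matches the NEWS-2 described in the protocol. New confusion should score 3 in the consciousness row, as Section 7.13.1 states, and the chart should include the SpO2 scale 2 cited in Sections 5.1.1, 8.1.1 and 11.5.1. Correct the chart title to match, and state in Section 7.13.1 that all sites score from that chart. With a second saturation scale on the page, the protocol should also say which one counts toward the endpoint score.

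If the eCRF records the components, derive the total from them, so that the scoring rule is applied once and in the same way for every site.

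The cost is one replaced table and a sentence or two of text. No patient assessment is added. The change is best made before scores are collected: where only A or a total has been recorded, the confusion item cannot be recovered from that record.

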## WHO COVID Ordinal Scoring Scale

*Ordinal Scale for Clinical Improvement (see Appendix 2)*

### CHEST CT-Scan (or in exceptional cases, chest radiogram)

All patients enrolling in the study will undergo a baseline Chest CT-Scan, among other assessments, in order to support the diagnosis and verify complete fulfillment of the inclusion criteria.

Several different patterns should be considered as possibly being related to SARS-CoV-2 infectious pneumonia (*from current published experience*):

- Ground-glass opacity ( $\geq 50\%$ ),
- Bilateral patchy shadowing ( $\geq 50\%$ ),
- Local patchy shadowing (30-50%),
- Interstitial abnormalities (10-25%).

A CT-Scan could be performed at Day 1 (24 hrs) and Day 4 and/or any time thereafter depending on the patient's disease course.

The surface area of lesions should be recorded and compared across all examinations from baseline onwards.

### Soluble GPVI

Soluble GPVI (sGPVI) levels will be measured in aliquots of frozen citrated platelet poor plasma (PPP) using a sandwich immunoassay using the MesoScale Discovery (MSD) technology.

**The concentrations will be extrapolated from standard curves generated by serial dilutions of recombinant GPVI ectodomain into 5% vol/vol GPVI depleted plasma (see section 7.12.2).**

### AE and SAE

All AEs experienced during the trial will be recorded in the patient's medical charts and they will be reported in the eCRF in accordance with the AE reporting described in [Section 9.6](#). AEs may be spontaneously reported by the patient or elicited as a result of general questioning by the study staff. Whenever possible, symptoms should be grouped as a single syndrome or diagnosis.

AEs of special interest (AESIs) will comprise the following:

- Bleeding-related events
- Thrombotic events

- Hypersensitivity events

Reference for these events is the last available version of the Meddra dictionary.

Occurrence and follow-up of AE should be assessed at each visit, and essential data listed hereafter should be recorded in the patient's eCRF and patient's medical file as well:

- the description of the AE;
- the seriousness of the event;
- the onset and end dates of the AE, including the time to onset since the last IMP infusion (if less than 24 hrs);
- the severity or grade of the AE;
- the causality with regards to study drug (glenzocimab or placebo);
- the action(s) taken regarding investigational product;
- the corrective treatment/therapy given;
- the event outcome.

### Laboratory tests

All clinical laboratory analyses will be performed at the local laboratory of the investigational site complying with good clinical practice (GCP) and local requirements.

At any time during the study, abnormal laboratory parameters deemed clinically relevant by the investigator (e.g., require delay in administration or discontinuation of study drug, lead to clinical symptoms or signs, or require therapeutic intervention or a change in concomitant treatments), whether specifically requested in the protocol or not, must be recorded as an adverse event on the appropriate section of the eCRF.

Following assessments will be performed at the local laboratory as described in the flowchart:

- Hematology: Hemoglobin, and platelet counts;
- Coagulation: INR, aPTT, PT;
- Biological markers: D-dimers, C Reactive Protein (CRP), Troponin T (TnT), Fibrinogen, IL6, NT proBNP, Pro-calcitonin, Ferritin
- Blood chemistry:
  - Renal function tests: Glomerular Filtration Rate (GFR), Urea;
  - Other: Serum glucose, LFTs (ASAT, ALAT), LDH.
- Urine or serum ( $\beta$ -hCG) pregnancy test for women of child bearing potential.

All laboratory tests performed as part of standard of care or for assessment of a possible AE outside of the scheduled visits will be collected as unscheduled assessments.

